There are no randomized trials on the use of this solution to prevent adhesions after ASIO operation currently present in the medical literature.

The current clinical study evaluates the safety and effectiveness of Icodextrin 4% for decreasing the incidence, extent, and severity of adhesions in patients after abdominal surgery for ASIO.

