**Figure 1 F1:**
[figure not shown]

The patients are followed-up for 5 years.

In case of reoperation for ASIO the procedure is carried out by a third party blinded to the patient's previous antiadhesive treatment: this surgeon evaluates incidence, location, severity, and extent of adhesions. The incidence of adhesions is assigned a severity score of 0 [no adhesions], 1 [filmy thickness, avascular], 2 [moderate thickness, limited vascularity], or 3 [dense thickness, vascularized].

Adverse events [AEs] are collected for the duration of the study, beginning at the time of randomization.

AEs are identified and described by the primary investigators.

In the control group, patients will be treated as in our daily surgical practice.

In the informed consent form, patients receive all the information about the study protocol, confidential data management and they fill up a questionnaire before signing or refuse.

There are not inconveniences caused to the patients. No incentives are planned for the patients regarding the operation or the follow-up.

There are not any additional risks for the treatment and control group: both groups have the standard surgical treatment and follow-up: icodextrin group is an antiadherences fluid with no adverse effects.

All the medical information obtained from the patients are kept confidential among the research scientists conducting the study.

The patients are free to withdraw from the study, whenever they want and without any obligation.

The study is approved by the ethical Committee of the S'Orsola-Malpighi Hospital, Bologna, Italy

The primary endpoints of our study are:

To evaluate the therapeutic role of Icodextrin 4% to reduce ASIO incidence

To reduce adherences rate [in case of reoperation for ASIO]

The onset of any other complications are recorded intraoperatively, postoperatively, at discharge, at 7-days, 1-month, 6-months, every year up to 5 years follow-up.

The primary outcomes are assessed every year [interim analysis] up to 5 years after the last enrolled patient.

The data generated by this study are analysed in two ways. The continuous numerical data are subjected to analysis of variance [ANOVA], this method being applicable to the discrimination of two continuous populations. Discrete data are analysed by the chi-squared test or Fisher exact test, as appropriate. Statistically significant differences between study treatments are based on p < 0.05.

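### The ordered 0–3 adhesion score has no order-respecting test: under the protocol's rule for discrete data the ordering would be ignored, at a moderate cost in power

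*Protocol article*

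**What the plan says.** All but one of the relevant statements stand in the Methods, in the text after Figure 1.

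- **The measurement.** A blinded surgeon assesses adhesions in patients reoperated for adhesive obstruction: "The incidence of adhesions is assigned a severity score of 0 [no adhesions], 1 [filmy thickness, avascular], 2 [moderate thickness, limited vascularity], or 3", with 3 the dense, vascularized grade. The levels are ordered.
- **The endpoint.** The second of two primary endpoints is "To reduce adherences rate [in case of reoperation for ASIO". It mentions neither the score nor severity.
- **The aim.** The Introduction gives the purpose as "decreasing the incidence, extent, and severity of adhesions in patients after abdominal surgery for ASIO".
- **The analysis.** "The data generated by this study are analysed in two ways". First, "The continuous numerical data are subjected to analysis of variance [ANOVA". Second, "Discrete data are analysed by the chi-squared test or Fisher exact test, as appropriate". The criterion is "Statistically significant differences between study treatments are based on p < 0.05".

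No rank, trend or ordinal-model method is named. No sentence says which of the two routes the severity score takes.

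**The concern.** A four-level grade falls most naturally under the rule for discrete data. A Pearson chi-squared or Fisher test on a table of arm by grade gives the same p-value however the grades are relabelled. It therefore spreads its sensitivity over patterns that nobody expects, when the question is whether icodextrin moves patients towards milder grades. The 2 × 4 table uses 3 degrees of freedom, while a rank or trend test puts everything on one contrast.

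The number of scored patients will be small, because only those reoperated for adhesive obstruction contribute, so lost efficiency matters.

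The undefined endpoint adds to the problem. If the rate means present versus absent, chi-squared or Fisher suits it. But a patient reoperated for adhesive obstruction is likely to have adhesions in either arm, so that rate would probably be high in both and tell little. If the endpoint is meant to use the grades, the ordering carries most of the information.

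**Working it through.** **1. The plan's own figure.** Inputs from Methods: 50% v 25% recurrence, 95% confidence, 80% power, 65 analysable and 88 enrolled per group. Two-sided testing is assumed.

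Without continuity correction: n = [1.96·√(2·0.375·0.625) + 0.842·√(0.5·0.5 + 0.25·0.75)]² / 0.25² = 57.7.

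With continuity correction: (57.7/4)·[1 + √(1 + 4/(57.7·0.25))]² = 65.4, which matches the stated 65. The step to 88 implies a loss of 1 − 65/88 = 26.1%. This calculation concerns recurrence. No sample size or power is given for the adhesion score.

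**2. How many patients could be scored.** The share of recurrences that are reoperated is not given.

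- All reoperated, no loss: 88 × 0.50 = 44 v 88 × 0.25 = 22. This is the upper limit on the plan's assumptions.
- All reoperated, 65 analysable: about 32 v 16.
- Half reoperated (assumed): 22 v 11, or 16 v 8.

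**3. Power by simulation, two-sided 5%.** The distributions are assumptions. Take control grades 0–3 as 10/25/35/30% and multiply the cumulative odds of a lower grade by 3. For example, P(grade 0) = 0.10 has odds 0.111; three times that is 0.333, or 0.25. The icodextrin grades become about 25/37/26/12%. The rank-sum test is tie-corrected, using the normal approximation.

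| Scored, control v icodextrin | Chi-squared | Rank-sum | ANOVA on the 0–3 score |
|---|---|---|---|
| 44 v 22 | 45% | 63% | 63% |
| 32 v 16 | 34% | 49% | 49% |
| 22 v 11 | 24% | 35% | 36% |
| 16 v 8 | 16% | 28% | 29% |

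The exact version of Fisher's test for the 2 × 4 table has 34%, 25% and 16% at the last three sizes, about the same as chi-squared.

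**4. Other assumptions.**

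- *Score 0 empty.* Grades 1–3 at 20/35/45% v 45/35/20% (odds ratio about 3.3): 59% v 69% at 44 v 22, 32% v 39% at 22 v 11, and 25% v 29% at 16 v 8. A second pattern, 10/30/60% v 30/40/30% (odds ratio about 3.5 to 3.9), gives gains of about 5 to 9 points over the four sizes.
- *Larger shift.* Equal control grades (25% each), odds ratio 4, 22 v 11: 30% v 50%, a gain of 20 points.
- *Smaller shift.* Control 2/18/35/45%, odds ratio 2: 10.6% v 13.8% at 16 v 8, and 8.1% v 10.2% at 10 v 5, so gains of about 3 and 2 points.
- *No effect.* Type I error is about 3% to 5% for chi-squared and 4% to 5% for rank-sum. Neither is inflated.

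For odds ratios of about 3 to 4 and 16 v 8 to 44 v 22 scored, the loss ranges from about 4 points (three grades in use, smallest sample) to about 20 points (four equally used grades, odds ratio 4).

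**The case against.** A reader might infer that the protocol tests a primary endpoint with the wrong test. The document does not support that, for four reasons.

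- **The score is not stated to be the primary endpoint.** The endpoint line speaks of a rate, which reads naturally as present versus absent, and the planned tests fit that. The score's description links incidence to severity, and severity is an aim, so the connection is plausible, but it is an inference. That the present/absent rate would be high in both arms is likely on clinical grounds; the document gives no figure, and its scale includes a grade for no adhesions.
- **The score is not stated to go to chi-squared or Fisher.** If it were treated as numerical it would go to ANOVA, which uses the ordering and loses almost nothing against the rank test (table above). The wording also does not exclude a chi-squared test for trend. However, the protocol reserves ANOVA for continuous data, so discrete is the likelier route. An open choice between routes is itself a reason to name one.
- **The detail may belong to the analysis plan.** An article condenses, and the test for each variable is often fixed elsewhere. What remains is that this article states a two-way rule with no place for ordered data. Changing it improves a stated method.
- **The planned test is valid.** Only efficiency is at issue, and power is low in most scenarios with either test. Nor is direction lost: grade proportions by arm would show it.

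A better test also leaves a larger limit in place. Grades exist only for patients reoperated after randomisation, and the plan expects treatment to change who recurs.

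**Conclusion.** The point holds as a moderate, inexpensive improvement. The protocol has an ordered score and an aim that names severity, but no method that uses the ordering, and it leaves unclear how the score relates to the primary adhesion rate. If the discrete-data rule is applied to the score, the result is valid but less sensitive: about 4 to 20 points of power lost for odds ratios of about 3 to 4 with 16 v 8 to 44 v 22 scored, and as little as about 2 points for a smaller shift in a smaller sample. These sizes rest on assumed grade distributions, proportional or near-proportional shifts in one direction, and an assumed reoperation share. The qualitative point does not depend on the exact values. It does not follow that the planned test is invalid, or that a rank test would turn the comparison among reoperated patients into an unbiased randomised effect.

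**What to change.** In the endpoint and statistics text of the Methods:

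1. State that the adhesion outcome at reoperation is the ordered 0–3 severity score. If a present/absent rate is also wanted, define it separately.
2. Compare arms on the score with an exact Wilcoxon rank-sum test, or a trend or proportional-odds analysis. Report an effect estimate (the probability of a lower grade, or a common odds ratio) with its 95% CI.
3. Keep chi-squared and Fisher for binary outcomes.
4. Report the comparison as conditional on reoperation, give the number reoperated in each arm beside it, and say that it is not to be read as an unbiased randomised effect.

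This costs a few sentences. No extra data or patients are needed, and the same analysis serves whether the score is primary or secondary.
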